## Methods

### Study design

The PerfectFit study is a cluster randomized control trial [29] (cRCT) among employees of three organizations, aimed to compare two groups: a purely internet-based approach (*limited or control* intervention) and a group that is exposed to the internet-based approach supplemented with MI (“the blended approach”, *extensive* intervention). The internet approach consists of a web-based HRA (later addressed as “HRA“) with tailored and personalized advice for health behavior change as well as pros and cons of the options for change. In the extensive intervention, the HRA is supplemented with face-to-face care provided by an (in-house) occupational physician (OP) using MI. The elements of the intervention are based on existing modules, previously evaluated RCTs [22, 30–32] and a recent meta-analysis [33]. Measurements were done at baseline and will be repeated after 6 and after 12 months.

Participants were included between 2012 and 2014 after providing written informed consent. There were no risks associated with participating in PerfectFit. Confidentiality was guaranteed during the study for all participants, as no information about the cardiovascular risk profiling, the HRA, or the coaching was provided to others than stated in the Participant Information Form. Ethical approval was obtained from the Medical Ethical Committee of Erasmus MC Rotterdam (METC) by registration number MEC 2012–459. The trial was registered on November 14^th^ of 2014 at the Netherlands Trial Register by registration number NTR4894.

After trial commencement, three OPs withdrew because of other priorities in work or due to personal issues, resulting in the loss of one military cluster and less inclusions than expected. In order to achieve sufficient power, we obtained approval of the METC to include an additional organization (i.e., an academic hospital).

### Study setting

The study is being performed among employees of three Dutch organizations: the military force, the police force, and an academic hospital. All organizations have an in-company occupational health center. Prior to the start of PerfectFit, all involved OPs of these health centers were introduced to the design and the goals of the PerfectFit study.

### Study population

The study population consisted of military personnel of ten Dutch military bases in different geographical regions in the Netherlands (*n* = 4207), executive personnel of three units of the police force in the western, central, and northern part of the Netherlands (*n* = 4086), and all health professionals of six wards (intensive cares and emergency rooms) of an academic hospital (*n* = 207). Based on previous data of 10,624 employees from a range of companies [34], we estimated 57.3 % (*n* = 5444) to be eligible, based on having at least one of three risk factors (obesity, smoking, lack of physical activity).

An entry point for recruitment of the study population was cardiovascular risk profiling (later in text: cardio screening). In the military force, all military employees of 40 years and over are expected to have this cardio screening once every three years. In the other two organizations, this type of screening is voluntary.

### Recruitment of participants

Aiming for optimal participation and commitment among participants and OPs, we obtained endorsement for this intervention study from both the boards of directors and the workers’ councils to perform this study. Recruitment in the military force started in 2012, in the police force in 2013, and in the hospital in 2014. Follow-up measurements will be completed by October 2015.

Information on the cardio screening and the PerfectFit study was repeatedly given in different formats (e.g., intranet publications, organizational magazine, and PerfectFit flyers, that were given out to applicants to the cardio screening). In the hospital, an additional information session was organized for the managers of the participating wards. Employees who were 40 years or older received the PerfectFit-flyer and a letter of invitation for the cardio screening signed by the highest manager. Participation in the PerfectFit study was voluntary and free of charge. The cardio screening and coaching sessions could be done during working hours, in contrast to completing the HRA and undertaking any individually chosen health activities.

### Inclusion criteria for the study

Participants in this study were 40 years and older who presented with at least one CVD risk factor during the baseline cardio screening. The age group 40 years and older was chosen for two reasons. Firstly, cardiovascular risk scores such as the Framingham Risk Score [35] and the European SCORE function start at the age of 40. Secondly, cardio screening is mandatory for military personnel in this age group [36]. The screening was performed by the OPs of the participating health centres.

The cardio screening consisted of three components: (1) a short questionnaire with questions related to personal lifestyle and family history; (2) anthropometric measurements; and (3) blood measurements. In a face-to-face session, the OP provided “usual care”-advice according to the applicable Dutch guidelines [37].

The short questionnaire used in the cardio screening consisted of eight questions on health behavior such as smoking (yes, no); meeting the Dutch physical activity norm of exercising five times a week at moderate intensity for at least half an hour (yes, no); family and personal history of cardiovascular diseases (yes, no), such as suffering from atrial fibrillation (yes, no); a first degree family member with angina pectoris or a history of heart attack (yes, no); and ever being diagnosed with diabetes (yes, no) or hypertension (yes, no). Participants were also asked whether they were being treated with prescription drugs for hypertension or heart problems (yes, no).

For blood pressure, weight, height and serum measurements, the OPs or their assistants used the instruments that are available for their daily practice. These instruments could vary between OPs, but were the same throughout the study. Systolic and diastolic blood pressures (in mmHg) were measured twice in a seated position at rest, and average blood pressure values were used. Waist circumference was measured halfway between the lower rib and the iliac crest, as is advised by the Dutch obesity recommendations for general practitioners [38]. Serum was analysed for total cholesterol, HDL, LDL, triglycerides (mmol/l), and glucose (mmol/l). If the glucose level exceeded 11.1, then also HbA1c (%) was measured.

These three components of the cardio screening provided entry points for the study, as it was used to identify employees at high risk for CVD. Inclusion criteria were met if a person had at least one of the following risk factors for CVD:Angina or myocardial infarction in first degree relatives;Physical inactivity, i.e. not meeting the guideline of physical activity at moderate intensity less than 30 min a day for 5 days per week or comparable effort;Smoking;Self-reported diabetes mellitus or random glucose ≥ 11.1 mmol/l;Obesity, defined as BMI ≥ 30 kg/m^2^ and / or waist circumference ≥ 102 cm for men or BMI ≥ 30 kg/m^2^ and/or ≥ 88 cm for women.Hypertension (diastolic value > 90 mm Hg or a systolic value > 140 mmHg) or the use of antihypertensive drugs;Dyslipidaemia (total cholesterol ≥ 5 mmol/l or LDL cholesterol ≥ 2.5 mmol/l or triglycerides: ≥ 1.7,mmol/l or HDL cholesterol: ≤ 1.0 mmol/l).

Employees who met the above mentioned inclusion criteria were excluded from participation if they had (1) manifest CVD (history of myocardial infarction, heart failure, or cerebrovascular accident); (2) a terminal illness; or (3) a history of psychosis. A flowchart of participants is shown in Fig. 1.

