**Methods:**

PerfectFit is a cluster randomized controlled trial, consisting of two arms. Based on cardiovascular risk profiling, done between 2012 and 2014, we included employees based on one or more risk factors and motivation to participate. One arm is the ‘limited’ health program (control) that consists of: (a) an HRA as a decision aid for lifestyle changes, including tailored and personalized advice, and pros and cons of the options, and (b) a newsletter every 3 months. The other arm is the ‘extensive’ program (intervention), which is additionally offered MI-sessions by trained occupational physicians, 4 face-to-face and 3 by telephone, and is offered more choices of health promotion activities in the HRA. During the follow-up period, participants choose the health promotion activities they personally prefer. After six and twelve months, outcomes will be assessed by online questionnaires. After twelve months the cardiovascular risk profiling will be repeated. The primary outcome is self-reported general health. Secondary outcomes are self-reported work ability, CVD-risk score, sickness absence, productivity loss at work, participation in health promotion activities, changes in lifestyle (smoking, alcohol consumption, physical activity, stress management) and body mass index. Furthermore, a process evaluation and an economic analysis will be performed.

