#### Obesity

Obesity, measured with waist circumference (in cm) and Body Mass Index (BMI,kg/m2), was determined at baseline and will be repeated at 12 month follow-up.

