### Randomization, blinding, and allocation to interventions

Military bases, regional police forces, and hospital wards were randomly assigned as ‘clusters’ to one of the two intervention groups. A total of 18 clusters were randomized, which were equally divided in 9 clusters that were allocated to the limited intervention and 9 clusters that were allocated to the extensive intervention. In each of these clusters, one or more OPs were assigned to contribute to PerfectFit, based on shown interest. We chose for a cluster design to ensure that the OPs were only active within a single study arm. The organizational unit was the preferred cluster for two reasons. First, OPs from the same organizational unit were all trained to execute the intervention so that discussions among colleagues would not bias the results. Second, grouping participants from the same organizational unit into the same intervention group will prevent so-called “contamination effects” among participants, i.e., talking and sharing experiences about involvement in two different types of interventions, which might influence their behaviors [69, 70].

In the military force we constructed ten clusters consisting of military ground force army bases located in different regions in The Netherlands. Since the police force was facing a large reorganization with possible replacements of OPs from one organizational unit to another, only two clusters could be constructed, based on organizational units in different regions. Randomization in the academic hospital was performed at the ward level, creating a total of 6 clusters.

For all organizations, the OPs only perform work for the health center within that particular organizational unit. Clusters were ordered according to their sizes, i.e. the number of potential eligible participants. For each pair of clusters of similar size within one organization, one of the clusters was randomly allocated to the extensive intervention and the other to the limited intervention. Randomization took place after an OP from the unit had confirmed participation, and prior to the inclusion of individual participants. A researcher who was not otherwise involved in the trial used version 3.0.1 of The R Foundation for Statistical Computing for the randomization. Researchers, participating OPs, and participants were not blinded for the group allocation, since this was impossible given the nature of the intervention and the cluster design.

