Our study design is unique for both its blended design of the intervention using a qualified decision aid and the follow-up at 6 and 12 months, which enables us to evaluate not just the initiation of health activities [9] but also the sustainability of lifestyle changes [81]. A second strength is the target population of employees in highly demanding jobs from three types of working organizations, whose workplace productivity and sickness absence might benefit from our intervention. Another strength is that the intervention is implemented within existing health centers and by their own OPs, improving external validity and making the results generalizable to larger companies. For the purpose of this study, a large investment was done for the OPs to master MI, which will remain beneficial to the organizations after completion of the study. Both the OPs from the extensive group and those from the limited group (after completion of the study), are educated to use the MI-technique, and skills they acquire and master during the time of the study and immediately afterwards can be internalized and incorporated in their everyday practice with all employees. From the perspective of the organization and society, these investments may pay off in the long run: an economic evaluation will be performed to analyze whether this truly is the case.

The study has three primary limitations. First, the effects on lifestyle changes may be affected by the healthy volunteer bias, since the study sample consists of employees of organizations who were actively recruited and who volunteered to participate [82]. Although we found differences in characteristics between organizations (Table 1), the potential bias will effect both the intervention and limited group alike, and will not have a large effect on our results (Table 2). Second, an attrition bias may occur at the follow-up measurements since those who achieve lifestyle changes might be more willing to do the final assessment than those who do not [83]. We will try to prevent this by sending personal invitations for final measurements by the OPs and having the OPs stimulate the participant to also fill out the questionnaire. A third issue is that blinding of the OPs, the participants and the investigators would have been preferred but could not be done in this real-life pragmatic trial.

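### An unblinded occupational physician, in the extensive arm possibly the participant's own coach, may take the 12-month weight, waist and blood pressure, so these secondary outcomes are open to differential assessor bias

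*Protocol article*

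**What the plan says.** The section on inclusion criteria describes the baseline cardio screening: "The screening was performed by the OPs of the participating health centres". On the blood pressure, weight, height and serum readings it adds that "the OPs or their assistants used the instruments that are available for their daily practice". On equipment: "These instruments could vary between OPs, but were the same throughout the study". Waist is described in a separate sentence that fixes the landmark but names no measurer.

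The abstract says of follow-up: "After twelve months the cardiovascular risk profiling will be repeated". The Obesity section says that waist and BMI "was determined at baseline and will be repeated at 12 month follow-up". The CVD-risk score section plans three scores at baseline and 12 months.

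Under Extensive intervention, trained OPs run seven coaching sessions and receive feedback on recorded sessions. Under Randomization, blinding, and allocation to interventions, each OP works in one arm only, and: "Researchers, participating OPs, and participants were not blinded for the group allocation, since this was impossible given the nature of the intervention". The Discussion repeats that blinding could not be done. To limit attrition it also plans "sending personal invitations for final measurements by the OPs".

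**The concern.** BMI, waist and blood pressure are measured rather than reported by the participant, so readers will look to them for support in an unblinded trial whose primary outcome is one self-rated health item. The Discussion itself leans on waist for an accurate estimate of obesity. That support weakens if the person taking the reading has spent a year coaching towards a better one.

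The stated reason for not blinding is sound for participants and coaches. It does not explain why measurement should stay with the coach, since the article itself says that assistants may take readings. Adjusting for baseline would not remove the problem, because the coaching relation arises after baseline.

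**Working it through.** **What the text permits.** The plan states no figure on this point, so the first check compares its statements.

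1. Who measured at baseline: OPs performed the screening, and OPs or assistants took the readings (Inclusion criteria for the study).
2. Who measures at 12 months: not named. Unchanged instruments and OP invitations to the final measurements suggest that the same centres measure again. This is an inference.
3. Who knows the arm: every OP in both arms, because each works in one arm and none is blinded.
4. Who coaches: OPs in the extensive arm only.
5. Safeguards: two seated blood-pressure readings are averaged, the waist landmark is fixed, and instruments do not change. Nothing separates coaching from measuring or keeps baseline values out of view.

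An unblinded OP may thus measure in either arm. Only in the extensive arm may that OP also be the coach.

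**Which outcomes are exposed.** Weight (hence BMI), waist and blood pressure are operator readings. Blood pressure enters SCORE and carries through to the Framingham score and QRISK2; QRISK2 also uses BMI. Age, sex, serum cholesterol and medical history are not operator readings. The primary outcome is a questionnaire item.

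**How much a shift would matter (illustration).** Let *b* be the difference between arms in mean measurement shift, in SD of the 12-month change. The documents give neither *b* nor that SD, so the range 0.1 to 0.3 is an assumption.

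- Participants: 217 limited and 274 extensive (Results). With the plan's 30% loss: 217 × 0.7 = 151.9 and 274 × 0.7 = 191.8, total 343.7.
- Clusters: 18 randomized less 1 lost = 17, so mean size is 343.7 / 17 = 20.2.
- Intra-cluster correlation: 0.05, the plan's value for general health, assumed to apply here.
- Design effect: 1 + (20.2 − 1) × 0.05 = 1.96.
- SE = √[1.96 × (1/151.9 + 1/191.8)] = 0.152 SD.
- Rejection rate with no true effect = 1 − Φ(1.96 − b/SE) + Φ(−1.96 − b/SE).

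| Shift *b* (SD) | b/SE | Rate, ICC 0.05 | Rate, ICC 0 (SE 0.109) |
|---|---|---|---|
| 0.1 | 0.66 | 10% | 15% |
| 0.2 | 1.32 | 26% | 45% |
| 0.3 | 1.97 | 51% | 79% |

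The nominal rate is 5%. This is a normal approximation; a t reference for 17 clusters would lower the rates somewhat.

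Only the difference between arms counts. If half the extensive-arm readings were shifted by 0.2 SD and none in the limited arm, then b = 0.5 × 0.2 = 0.1 and the rate is 10%. If both arms shifted equally, b = 0 and the rate stays at 5%.

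**The case against.** The strongest reply is that this reads silence in a condensed article. The sentences on measurement are in the past tense and describe the entry screening. The instrument sentence does not list waist. The OP invitations concern attrition. A full protocol or site manual may well name the 12-month assessor. This stands as far as it goes: that the coach measures at follow-up is an inference, and the point is only that the text allows it.

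A reader might infer that the bias sits in one arm only. The documents do not support that, because OPs in both arms are unblinded and may measure their own participants. What is confined to the extensive arm is the possible overlap of coach and assessor, so the risk is differential rather than one-sided.

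The measurement rules also narrow discretion: averaging limits selective choice of a blood-pressure reading, and the fixed landmark limits tape placement. They reduce the room for bias without removing it.

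The article already lists lack of blinding among its three main limitations. That disclosure covers OPs, participants and investigators in general and does not treat outcome measurement separately.

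Two objections to the remedy hold. Assistants in the same unit probably know the allocation too, so using them separates measuring from coaching but does not blind. And the article appeared on 28 July 2015 with follow-up to end by October 2015, so most 12-month readings had probably been taken.

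**Conclusion.** The concern holds as a possible differential assessor bias in BMI, waist, and the blood-pressure and BMI components of the CVD-risk scores. It rests on two facts in the text: OPs may take the readings, and OPs coach in the extensive arm. It also rests on one inference, that the screening is repeated under the same arrangement. The claim that blinding was impossible does not justify leaving measurement with the coach.

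The size is unknown. The illustration shows that a modest differential shift would matter, not that one exists. A reader might go further and conclude that the CVD-risk results as a whole, or the trial's main result, are compromised. The documents do not support either conclusion: the scores are only partly exposed, and this route touches neither the self-reported primary outcome nor the serum values. It is a worthwhile, inexpensive improvement to secondary outcomes. Given the dates, most of its value lies in analysis and disclosure.

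**What to change.** 1. **Remaining 12-month visits, both arms.** Where an assistant is available, have the health-centre assistant rather than the participant's own OP take weight, waist and blood pressure, without baseline values in view. Record who measured.
2. **All visits where the measurer is known.** Repeat the obesity and CVD-risk analyses without OP-measured readings, and show by arm and cluster how many readings remain.
3. **Reporting.** Present laboratory lipids alongside, as components not open to this bias.
4. **Limitation.** State that OPs in either arm, including coaches in the extensive arm, may have taken these readings, that this concerns the secondary outcomes named above, and that assistants may also have known the allocation.

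The cost is one site instruction, one data field and some scheduling effort where the OP usually measures. The sensitivity analysis will have a smaller sample and could lose whole centres out of 17 clusters, so it should be read as a check on the main secondary analyses and not as a replacement. The measurer may not be recoverable for visits already completed; for those, only the disclosure applies.

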**Fig. 1 Fig1:**
[figure not shown]
Flow of clusters and participants until allocation within the trial

### Study interventions

After the cardio screening at baseline, employees who were included in both the extensive and the limited study intervention groups, were invited by the OP to log on to the web-based HRA, by giving them a personal voucher-code.

#### Web-based HRA

The web-based HRA consists of a web-based electronic questionnaire, including questions on lifestyle, work, family history, medical history, and motivation to change, which takes 30 to 45 min to fill out. Based on the answers on these questions, as well as on the baseline anthropometric and blood measurements that are integrated in the online system, the web-based HRA generates tailored and personalized advice to the participant, which are presented as low-risk (green), intermediate-risk (orange), or high-risk (red) profiles. Personalized advice includes a suggestion of choice out of health promotion activities, based on the participant’s risk profile, preferences and motivational aspects, according to the transtheoretical model of health behavior change [39]. These optional choices can be selected from a list of activities that are “usual care” for each organization. Prior to the inclusion period, this list was constructed by the OPs and the research team, and it includes health promotion activities on lifestyle items (i.e. sports facilities, dietician, psychologist). This web-based HRA can be considered as a patient decision aid, since it meets the six qualifying criteria [40]. The flowchart of the intervention is shown in Fig. 2.

